### Participants

The target population in the study will be University students who have academic-related psychological problems. The inclusion criteria of the sample are a University student, aged 18–25 years old, having academic-related problem(s), and registering as a participant in this study. The academic-related problems that will be included in the study are (1) (educational) adjustment difficulties; (2) difficulties in writing a thesis; (3) academic procrastination; (4) poor self-regulation for learning; and (5) a low grade point average (GPA). The study will exclude students with (1) physical disabilities; (2) under the care of mental health professionals; and (3) the score of PHQ-9 more than 14 (having severe depression), (Rahmadiana et al., 2019).

The participants of the study will be those who register in a University counseling center. They will be then screened with the PHQ-9. If they are willing to participate in the study, the research assistants will give informed consent and the right to withdraw from the study at any given time they wish to. The students who decline to join the study or withdraw from the study will be followed up to identify their reasons for declining and withdrawing from the study. The students have a right to undergo post-trial treatment if needed.

The sample size is a sensitive issue in the non-inferiority trial (Hahn, 2012). Large sample size is usually needed. However, if the new intervention is assumed to be slightly more effective than the TAU, the number of samples can be reduced. The mobile-based counseling application can be assumed to be more practical for the students in this country. Those who live remotely can still access the psychological services. The data from the University counseling center in 2020 were also a source of consideration in determining the sample size. The center admitted 482 clients in that year, with an average of 40 clients per month. With 80% CI, the expected SD will be one, and the inferiority margin (Δ) will be 0.24. It was calculated that the number of participants per arm needs to be 215 and the total sample size needs to be 430.

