### Outcome Measurements

The participants in the intervention group will complete the assessments at (1) the baseline (T0); (2) at the end of the first counseling session (T1); (3) at the end of the second counseling session (T2); (4) at the end of the third counseling session (T3); and (5) 3 months after the third counseling session (T4). There will be a week interval between the counseling sessions (T1, T2, and T3). Meanwhile, the participants in the control group will be measured at 3–5 points in time depends on the number of counseling sessions they have. They will fill the questionnaires at (1) the baseline (T0); (2) at the end of their counseling session(s), (T1 and/or T2 and/or T3, etc.); and (3) 3 months after the last session (TX). The data will be collected using the online forms and will be assisted by the research assistants.

The primary outcome of the proposed study will be CSE measured by the Coping Self-Efficacy (CSE) Scale. The Indonesian version of the CSE consists of 26 items with 11-point scale (0–10). The scale has good reliability (*r* = 0.92), (Nurhidayah, 2020). The total score will be used as an indicator of the level of CSE of participants. The CSE is defined as a belief about own ability of an individual to perform specific coping behavior (Chesney et al., 2006). Self-efficacy serves as evidence in measuring changes in the coping ability of individuals, especially for those who seek professionals to solve their problems (Chesney et al., 2006; Yoo et al., 2020).

The secondary outcomes of this study will be (1) resilience and (2) level of depression. Resilience is defined as the capacity of a dynamic system to adapt successfully to adversity that threatens system function (Masten, 2014). The Resilience Scale (RS-14), (Surzykiewicz et al., 2019), which will be used to measure this variable, has five dimensions, namely, equanimity, perseverance, self-reliance, meaningfulness, and existential aloneness. The short version of the RS test has been adapted to the Indonesian language. It has 14 items with a 7-point Likert scale (*r* = 0.87). The scale has good Construct Validity Fitness Indexes [Non Normed Fit Index (NNFI) = 0.99, Root Mean Square Error of Approximation (RMSEA) = 0.027, and Standardized Root Mean Residual (SRMR) = 0.026], (Valentino, 2021).

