### Determining an Inferiority Margin of the Trial

In the non-inferiority trial, the researchers need to determine Δ (Hahn, 2012). In this study, the margin is the maximum acceptable extent of non-inferiority of the mobile-based counseling application. The maximum limit of Δ can be set to the entire effect size of the active control treatment (Hahn, 2012). Several proposals for choosing the inferiority margins in the context of SFBT have been made (Table 1). There are several suggestions for the maximum difference in outcomes that will be considered clinically irrelevant. It ranges from *d* = 0.17 to *d* = 1.76. The smallest margin was suggested by Schmit et al. (2016), (*d* = 0.24) for the treatment of internalizing disorders. Thus, in this study, it was decided to use the inferior margin of 0.22 (i.e., the inferior margin up to 0.22), corresponding to a small effect size.

**Table 1 T1:** The effect size from the solution-focused brief therapy (SFBT)-related studies.

**Previous studies**	**Effect size**
Impacts on academic and emotional difficulties (Daki and Savage, 2010)	≈0.13 (partial eta squared, medium effect size)
Meta-analysis of solution-focused brief therapy for treating symptoms of internalizing disorders (Schmit et al., 2016)	≈0.24 (Hedges' g, small effect size)
Examining the effectiveness of solution-focused brief therapy: a meta-analysis (Kim, 2008)	0.26–0.38 (Cohen's *d*, small effect size)
SFBT for health-related psychosocial outcomes (Zhang et al., 2018)	0.34 (Cohen's *d*, small effect size)
Solution-focused brief therapy in schools: A review of the outcome literature (Kim and Franklin, 2009)	0.38–1.76 (Cohen's *d*, medium to large effect size)

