### Data Analysis

Descriptive statistics will be used to describe relevant demographic data, such as the frequency and the percentage for the categorical data as well as the mean and the SD for the outcome measurements. There will be three analysis plans to prove the non-inferiority of the application, which are (1) repeated-measures ANOVAs (Goodman et al., 2016; Twisk et al., 2018), which will be used to test for differences between the TAU and the intervention groups (i.e., between-subjects factor) in the treatment at the four time points (i.e., within-subjects factor). We would like to assess whether the outcomes will be improved after treatment using the application and the TAU. An analysis will be conducted to check the constancy assumption. Then, both (2) the intention-to-treat (ITT) and (3) the per-protocol analysis will be performed. Previous studies showed that performing both analyses will produce more convincing results to conclude the non-inferiority of a new treatment (Hahn, 2012; Walker, 2019). The ITT analyses will be chosen to handle the missing value due to the protocol deviations, withdrawal, and non-compliance (Gupta, 2011) whereas the per-protocol analysis will minimize the factors that would make the two groups seem similar (Walker, 2019).

The statistical hypotheses in this non-inferiority trial use Δ. The null hypothesis states that the intervention using the application will be inferior to the TAU (H0: TAU–SAENA ≥ Δ). The alternative hypothesis states that the intervention will not be inferior (will have a similar effect) to the TAU although the effect may not be as good as the TAU within the extent of margin (H1: TAU–SAENA < Δ). Of note, 95% CI will be used. The interval will be the mean difference between the outcome measures of the two groups. The formula is as follows:

$$\begin{array}{l} \left(\mu_{saena}-\;\mu_{TAU}\right)\pm 1.96\sqrt{\frac{\sigma_{saena}^{2}}{n_{saena}}+\frac{\sigma_{TAU}^{2}}{n_{TAU}}} \end{array}$$

μ, mean; Tau, standard deviation; *n*, sample.

The 1.96 is the *z*-value, and the value from this formula can now be compared with Δ. If the interval remains above Δ, then the inferiority of the application will be proven according to the standards that have been set. In contrast, if the upper limit for treatment difference by the intervention group compared to the TAU group is < Δ, then the non-inferiority will be concluded.

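### The non-inferiority margin is in SD units, but the decision rule compares it with an interval in raw score points and names no SD to link the two

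*Protocol article*

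**What the plan says.** All references are to the protocol article.

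- **Margin.** The section on determining the inferiority margin draws on a table of published effect sizes, mostly Cohen's d and Hedges' g, and concludes: "it was decided to use the inferior margin of 0.22 (i.e., the inferior margin up to 0.22), corresponding to a small effect size".
- **Sample size.** The Participants section uses a different value, again in SD units: "the expected SD will be one, and the inferiority margin (Δ) will be 0.24". It arrives at 215 per arm, 430 in total.
- **Primary outcome.** Under Outcome Measurements, "The Indonesian version of the CSE consists of 26 items with 11-point scale (0–10"; and "The total score will be used as an indicator of the level of CSE of participants". The analysed score therefore runs from 0 to 26 × 10 = 260.
- **Decision rule.** Under Data Analysis, "The interval will be the mean difference between the outcome measures of the two groups". The printed formula is the difference of the two means plus or minus 1.96 standard errors, with the variances appearing only inside the standard error. The text then says that "the value from this formula can now be compared with Δ".

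No section standardises the outcome, divides the difference by an SD, or converts Δ into points of the CSE, RS-14 or PHQ-9.

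**The concern.** A margin and the interval it is compared with must be in the same units. Here Δ is a fraction of an SD and the interval is in questionnaire points. An analyst then has two ways to proceed, and both cause trouble.

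- **Follow the text.** Δ becomes about a quarter of one point on a 260-point scale, far narrower than the interval can be at this sample size. An app that is truly as good as usual care would nearly always fail the primary test.
- **Rescale without a stated rule.** The pass mark in points becomes Δ times whichever SD is picked: baseline or follow-up, one arm or pooled, trial or validation sample. The threshold is proportional to that SD, so choosing it after seeing the data means choosing the threshold after seeing the data.

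The rule decides the primary claim of the trial. The RS-14 (14 seven-point items) and PHQ-9 (nine four-point items) have the same mismatch.

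**Working it through.** **Inputs from the article.** Δ = 0.24 and SD = 1 (Participants); Δ = 0.22 (margin section); 215 per arm (Participants); multiplier 1.96, i.e. a two-sided 95% interval (Data Analysis); CSE total 0–260 (Outcome Measurements).

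**Assumed.** The SD of the CSE total, which the article does not give. I use 10 to 60 points.

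**Step 1: reproduce the plan's figure.** n per arm = 2(z₁₋α + z₁₋β)² / Δ². With Δ = 0.24, SD = 1, true difference 0, one-sided α = 0.05 and 80% power (reading the printed 80% as power): 2(1.645 + 0.842)² / 0.24² = 214.7, rounded up to 215. This matches exactly. With Δ = 0.22 the same formula gives 256. With one-sided 0.025, which is what 1.96 implies, it gives 273 for 0.24 and 325 for 0.22. So the 215 rests on Δ = 0.24 in SD units.

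**Step 2: width of the planned interval in points.** SE = SD × √(2/215) = 0.0964 × SD, so the half-width is 1.96 × SE = 0.189 × SD. It is below 0.24 only if SD < 0.24/0.189 = 1.27 points, and below 0.22 only if SD < 1.16 points.

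**Step 3: chance of showing non-inferiority with Δ read as points.** Direction TAU − SAENA, as in the hypotheses; true difference 0: Φ(Δ/SE − 1.96).

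| Assumed CSE SD (points) | 95% half-width (points) | Chance, Δ = 0.22 | Chance, Δ = 0.24 | 0.22 × SD (points) | 0.24 × SD (points) |
|---|---|---|---|---|---|
| 10 | 1.89 | 4.2% | 4.4% | 2.2 | 2.4 |
| 20 | 3.78 | 3.2% | 3.3% | 4.4 | 4.8 |
| 40 | 7.56 | 2.9% | 2.9% | 8.8 | 9.6 |
| 60 | 11.34 | 2.7% | 2.8% | 13.2 | 14.4 |

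The last two columns show the margin in points that a standardised Δ would imply.

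**Step 4: could the SD be near 1?** Take the stated CSE reliability of 0.92 as Cronbach's alpha for 26 items (an assumption). Then 0.92 = (26/25)(1 − 26s²/S²), which gives S ≈ 15.0 × s, where s is a common item SD and S the SD of the total. A total SD of 1.27 would need s ≈ 0.085 on an item scored 0–10. Item SDs of 1 to 2.5 give totals of about 15 to 37.5.

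**Step 5: secondary outcomes, same formula, Δ = 0.24.** RS-14 with an assumed SD of 8 to 15: 5.0% to 3.6%. PHQ-9 with an assumed SD of 3 to 5: 12.9% to 7.2%.

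**Step 6: power once the scales agree.** The SD cancels: Φ(Δ/√(2/215) − 1.96).

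- Δ = 0.22: Φ(2.281 − 1.96) = 62.6%
- Δ = 0.24: Φ(2.488 − 1.96) = 70.1%

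**The case against.** **The intended scale is visible.** Δ is described as an effect size, the sample size sets the SD to one, and the Discussion again speaks of a small effect. Few analysts would apply a quarter of a point to a 260-point scale. This stands as a reading of intent, and it makes informal rescaling the likelier course. It does not supply the missing element: the formula carries two group-specific variances and names no reference SD, so the threshold stays open.

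**The conversion may be in a fuller protocol or analysis plan.** It may be. But the article does not leave the matter open. It prints the formula, the margin and the comparison, and as printed their units do not match.

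**A reader might infer that non-inferiority is practically unattainable.** The documents do not support that without conditions, for three reasons:

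- The figure of about 3% assumes a true difference of zero. A clearly better app could pass: at SD 30 and Δ = 0.24, 80% power needs a true advantage of (1.96 + 0.842) × 2.893 − 0.24 ≈ 7.9 points.
- It assumes the direction of the hypotheses. The printed formula takes SAENA − TAU and requires the upper limit to be below Δ, so on the CSE, where higher is better, a worse app passes more easily. If the app were 0.27 SD worse, the chance is about Φ(0.27/0.0964 − 1.96) ≈ 80%, ignoring the tiny raw Δ. That sign conflict is a separate defect; at a true difference of zero the chance is the same either way.
- It rests on an assumed CSE SD, although any SD above a few points leads to the same conclusion. The near-zero chance does not carry over equally to the PHQ-9.

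**Conclusion.** The concern holds in this form: Δ is in SD units, and the decision rule compares it directly with an unstandardised difference in means. This is an error in a stated rule, not an omitted detail. Read literally, in the TAU − SAENA direction and with truly equal arms, the primary test succeeds about 3% of the time for an assumed CSE SD of 20 to 60 points, and about 4% at 10 points. Read as probably intended, the threshold depends on an SD that nobody has named; across assumed SDs of 20 to 60, Δ = 0.22 means anything from 4.4 to 13.2 points.

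It would also be wrong to infer that correcting the scale returns the trial to its planned 80% power. The 215 per arm needs Δ = 0.24 and a one-sided 5% level, whereas the analysis uses a 95% interval and the margin section uses 0.22.

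**What to change.** Before unblinding, amend the Data Analysis section as follows.

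1. **Settle one Δ.** Reconcile 0.22 with 0.24 and use the chosen value in the margin, sample-size and analysis text.
2. **Name one SD per outcome and put both quantities on one scale.** For the CSE this could be the blinded pooled baseline SD of the total. Either divide the difference and both confidence limits by that SD before comparing with Δ, or state the margin in points as Δ × that SD and compare the raw interval with it.
3. **Treat the PHQ-9 separately.** Entry is limited to scores of 14 or lower, so baseline scores are truncated and their SD may be too small a yardstick. Name an SD that takes account of this. Orient the difference so that lower scores count as better.
4. **Restate the power.** At 215 per arm with the 95% interval it is 62.6% for Δ = 0.22 and 70.1% for Δ = 0.24.

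For the scale itself, the cost is a few sentences and one calculation per outcome. The small downside is that a margin in points then depends on an estimated SD. Restating the power costs nothing to write, but it will show a shortfall from 80% that the scale correction does not remove.

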According to several studies, online counseling is needed by students because they cannot access mental healthcare (Chan, 2020; Li and Leung, 2020; Novella et al., 2020). Although there are several limitations, the studies showed that online counseling is effective in dealing with psychological issues such as emotional distress, anxiety, and social withdrawal symptoms. The study aimed to test whether or not the mobile-based counseling application called “SAENA” can help the students increase their (1) CSE and (2) resiliency, as well as decrease their (3) level of depression. Therefore, the hypothesis is that the application is equivalent to the Treatment-As-Usual (TAU) in increasing the personal resources of students.

The quality of a study depends on how well-both the design and execution phases of the project are (Ott, 1991). By writing the protocol, a gap between these phases could be examined carefully and fairly. The protocol also helps the researchers in providing study documentation as well as in increasing the efficiency of the projects (Ott, 1991). Therefore, this study will explain the protocol of the non-inferiority trial of the mobile-based counseling application.

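### The printed confidence-interval rule reverses the non-inferiority verdict for the primary outcome, coping self-efficacy

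*Protocol article*

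**What the plan says.** All of the following stands in the protocol article.

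- **Direction of the outcomes.** Outcome Measurements: "The primary outcome of the proposed study will be CSE measured by the Coping Self-Efficacy (CSE) Scale", and "The total score will be used as an indicator of the level of CSE of participants". The Introduction gives the aim as testing whether the application "can help the students increase their (1) CSE and (2) resiliency, as well as decrease their (3) level of depression". Higher is therefore better for CSE and resilience (RS-14), and lower is better for depression (PHQ-9).
- **Hypotheses.** Data Analysis: "H0: TAU–SAENA ≥ Δ" and "H1: TAU–SAENA < Δ". The contrast is TAU minus SAENA.
- **Interval.** The displayed formula in the same section takes the SAENA mean minus the TAU mean, plus or minus 1.96 standard errors. The text then says that the result of this formula is what is set against Δ.
- **Verdicts.** "If the interval remains above Δ, then the inferiority of the application will be proven". Non-inferiority is concluded "if the upper limit for treatment difference by the intervention group compared to the TAU group is < Δ".
- **Margin.** Δ is positive wherever it appears: 0.24 in the sample-size paragraph under Participants, and 0.22 in the section on determining the margin.

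No separate rule is given for each outcome.

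**The concern.** The contrast changes sign between the hypotheses and the interval, while Δ stays positive and the verdicts stay the same. For an outcome where higher is better, an interval for SAENA minus TAU lying wholly above +Δ means that SAENA beats TAU by more than the margin. The article calls that inferiority. An upper limit below +Δ is easily reached by an application that is much worse than TAU. The article calls that non-inferiority.

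Applied as printed, the rule would pass a harmful loss of CSE and fail a clear gain. The same holds for RS-14. For PHQ-9 the interval rule happens to point the right way, but the printed null hypothesis is then the reversed one. No outcome has hypotheses and a decision rule that agree.

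**Working it through.** **Inputs.** 215 per arm and SD = 1 (Participants); 1.96 and the contrast SAENA − TAU (Data Analysis); Δ = 0.22 (margin section) and Δ = 0.24 (Participants).

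**The article's own figure.** For a one-sided 5% level, 80% power (the article's 80% is called a confidence interval and is read here as power) and a true difference of zero:

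n per arm = 2 × (1.645 + 0.842)² / 0.24² ≈ 214.7, rounded up to 215, or 430 in total.

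This reproduces the stated size, so 215 per arm on the SD scale is a fair basis for the check.

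**Precision.** SE = √(2/215) = 0.0964. Half-width = 1.96 × 0.0964 = 0.189.

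**Printed rule on SAENA − TAU, Δ = 0.22.**
- Non-inferior if estimate + 0.189 < 0.22, that is, estimate < +0.031.
- Inferior if estimate − 0.189 > 0.22, that is, estimate > +0.409.
- For a true difference t: P(non-inferior) = Φ((0.031 − t)/0.0964) and P(inferior) = 1 − Φ((0.409 − t)/0.0964).

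**Rule that matches the hypotheses for CSE.** Non-inferior if the lower limit exceeds −0.22, that is, estimate > −0.031. P(non-inferior) = Φ((t + 0.22)/0.0964 − 1.96).

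| True SAENA − TAU (SD) | Printed: non-inferior | Printed: inferior | Matching rule: non-inferior |
|---|---|---|---|
| −0.50 | 100% | 0% | 0% |
| −0.22 | 99.5% | 0% | 2.5% |
| 0 | 63% | 0% | 63% |
| +0.30 | 0.3% | 13% | 99.97% |
| +0.50 | 0% | 83% | 100% |

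Two entries written out:
- At t = −0.22, printed rule: (0.031 + 0.22)/0.0964 = 2.60, and Φ(2.60) = 0.995.
- At t = +0.50, printed inferior: (0.409 − 0.50)/0.0964 = −0.94, and 1 − Φ(−0.94) = 0.83.

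**With Δ = 0.24.** The cut-offs become +0.051 and +0.429. The printed rule gives non-inferiority in 99.9% at t = −0.24 and in 70% at t = 0, and inferiority in 77% at t = +0.50.

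The two rules agree at t = 0, so a check made only under equality would not reveal the fault.

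**The case against.** The best defence is that this is a slip in one formula. The hypotheses and their verbal explanation have the right sign for CSE. Both verdict sentences are also right if the difference is read as TAU minus SAENA. Only the order of subtraction in the displayed formula is out of line, and an analyst who follows the hypotheses would reach the correct conclusion. This stands as a description of the likely intent, and it means the repair can be short. It does not remove the fault. The text names the result of that formula as the quantity to compare with Δ, and the non-inferiority sentence describes the intervention group relative to TAU. Nothing elsewhere in the article says which contrast prevails.

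A second point is that a better application does not always receive the inferior verdict. That is correct. At +0.30 SD about 87% of trials (100 − 0.3 − 13) would get neither verdict, and the false inferior verdict becomes likely only for true benefits near 0.5 SD. The false non-inferior verdict has no such limit.

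A third point is that PHQ-9 is secondary, and a full plan may set the direction for each outcome. That makes the PHQ-9 part the weaker one. The primary-outcome fault is a matter of what the article states, so an unseen plan would have to contradict it in order to correct it.

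**Conclusion.** The concern holds. As printed, the decision rule is inverted for CSE and for RS-14 and contradicts the hypotheses given in the same section. The probability of declaring non-inferiority when SAENA is worse by exactly the margin exceeds 99% with either margin, against the 2.5% implied by a two-sided 95% interval.

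The percentages assume 215 analysed per arm, a normally distributed estimate, SD = 1 and outcomes on the SD scale. The inversion is one of sign and depends on none of these. Because it governs the primary conclusion, it must be corrected before the data are analysed.

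**What to change.** State the direction for each outcome and use one contrast throughout.

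- **CSE and RS-14 (higher is better), on SAENA − TAU:** conclude non-inferiority if the lower 95% limit is above −Δ. Conclude inferiority only if the upper limit is below −Δ. Equivalently, swap the two means in the formula so that the interval is for TAU − SAENA; the existing verdict sentences then hold for these two outcomes.
- **PHQ-9 (lower is better), on SAENA − TAU:** write the null hypothesis as SAENA − TAU ≥ Δ, and conclude non-inferiority if the upper limit is below +Δ.
- If SAENA − TAU is kept, delete the general sentence that equates an interval above Δ with inferiority.

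While rewriting the paragraph, say how Δ meets the interval. Δ is a standardised effect, whereas the formula gives a difference in score points (CSE has 26 items scored 0 to 10). Either the difference must be standardised or Δ converted to points. The same paragraph should name a single margin, since 0.22 and 0.24 both appear.

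The sign correction changes the wording of one paragraph. It needs no extra participants, data or visits.

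### The interval is SAENA minus TAU, but non-inferiority is declared when its upper limit is below +Δ, which reverses the decision on the primary outcome

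*Protocol article*

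**What the plan says.** All references are to the protocol article.

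- **Outcome and direction.** Outcome Measurements: "The primary outcome of the proposed study will be CSE measured by the Coping Self-Efficacy (CSE) Scale", and "The total score will be used as an indicator of the level of CSE of participants". The Introduction gives the direction of benefit: the app is tested on whether it "can help the students increase their (1) CSE and (2) resiliency, as well as decrease their (3) level of depression". Higher CSE is therefore better. The same holds for resilience, and the opposite for the PHQ-9.
- **Hypotheses.** Data Analysis: "H0: TAU–SAENA ≥ Δ" and "H1: TAU–SAENA < Δ".
- **Interval.** The formula printed next in Data Analysis is centred on the SAENA mean minus the TAU mean, plus or minus 1.96 standard errors. The text says its result is to be compared with Δ and mentions no change of sign.
- **Decision rules.** Inferiority: "If the interval remains above Δ, then the inferiority of the application will be proven". Non-inferiority is concluded "if the upper limit for treatment difference by the intervention group compared to the TAU group is < Δ".

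Nowhere does the article give a −Δ bound, a rule on the lower limit, or reverse scoring of the CSE.

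**The concern.** The hypotheses and the interval use opposite signs. The decision rules suit the hypotheses' contrast, but they are applied to the interval's contrast.

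For SAENA minus TAU on a scale where higher is better, harm lies on the negative side. The lower limit is the one that rules harm out, and the bound is −Δ. A test of the upper limit against +Δ looks at the wrong end: the worse the app performs, the more easily it passes. An interval wholly above +Δ means the app beats usual counselling by more than Δ, yet the plan would then call it inferior.

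This is the decision rule for the primary endpoint. Applied as printed, it gives no protection against adopting an inferior app and would penalise one that outperforms usual counselling. The problem is separate from the units of Δ and from the orientation of the hypotheses for the PHQ-9, and it would remain after both were settled.

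**Working it through.** **Inputs**
- 215 per arm, SD 1, Δ = 0.24 (Participants, sample-size paragraph).
- Δ = 0.22 (Determining an Inferiority Margin of the Trial). The two sections differ, so both values are run.
- Multiplier 1.96 (Data Analysis), i.e. one-sided 0.025.

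**The plan's own figure.** The 80% is attached to a confidence interval in the text. Reading it as 80% power, with one-sided alpha 0.05 (not stated) and no true difference:

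n per arm = 2(1.645 + 0.842)² / 0.24² ≈ 12.37 / 0.0576 ≈ 214.7, rounded up to 215.

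This matches the article, so SD 1 and Δ in SD units are the working scale used below.

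**Standard error.** SE = √(2/215) = 0.0964; half-width = 1.96 × 0.0964 = 0.189.

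**Rules in terms of the observed SAENA − TAU**

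| Rule | Δ = 0.22 | Δ = 0.24 |
|---|---|---|
| Printed: non-inferior if observed difference < Δ − 0.189 | < +0.031 | < +0.051 |
| Printed: inferior if observed difference > Δ + 0.189 | > +0.409 | > +0.429 |
| Implied by the hypotheses: non-inferior if observed difference > −Δ + 0.189 | > −0.031 | > −0.051 |

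**Probabilities at true difference d = SAENA − TAU**
- Printed rule, non-inferior: Φ((Δ − d)/SE − 1.96)
- Rule implied by the hypotheses, non-inferior: Φ((Δ + d)/SE − 1.96)
- Printed rule, inferior: 1 − Φ((Δ − d)/SE + 1.96)

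Example, Δ = 0.22 and d = −0.22: printed rule Φ(0.44/0.0964 − 1.96) = Φ(2.60) = 0.995; implied rule Φ(0 − 1.96) = 0.025.

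| Δ | d | Printed: non-inferior | Implied: non-inferior | Printed: inferior |
|---|---|---|---|---|
| 0.22 | −0.50 | 1.000 | 0.000 | 0.000 |
| 0.22 | −0.22 | 0.995 | 0.025 | 0.000 |
| 0.22 | −0.10 | 0.913 | 0.237 | 0.000 |
| 0.22 | 0 | 0.626 | 0.626 | 0.000 |
| 0.22 | +0.10 | 0.237 | 0.913 | 0.001 |
| 0.22 | +0.30 | 0.003 | 0.9997 | 0.129 |
| 0.22 | +0.50 | 0.000 | 1.000 | 0.827 |
| 0.24 | −0.24 | 0.999 | 0.025 | 0.000 |
| 0.24 | 0 | 0.701 | 0.701 | 0.000 |
| 0.24 | +0.50 | 0.000 | 1.000 | 0.769 |

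A simulation of 20,000 trials per scenario at Δ = 0.24 agreed: 0.9991 declared non-inferior at d = −0.24, and 0.771 called inferior at d = +0.50.

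The two rules have the same probability of declaring non-inferiority only at d = 0. Even there they reach the same decision in a single trial only if the observed difference lies within ±0.031 (Δ = 0.22) or ±0.051 (Δ = 0.24), which is about 25% or 40% of trials.

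**The case against.** The strongest reply is that this is one sign slip, not a wrong rule. The hypotheses are correctly oriented for CSE, and both decision sentences are their natural companions. Exchange the two means in the formula and the rules work for CSE and the RS-14. The error probabilities arise only if an analyst follows the formula and ignores the hypotheses beside it. The planned repeated-measures ANOVA would also show which way the groups differ, and an app with higher CSE labelled inferior would probably be noticed.

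Much of this stands as a description of the cause, and it makes the repair easy. It does not remove the fault. The reversed direction appears in the formula and again in the verbal rule, which speaks of the intervention group relative to TAU, and the text tells the analyst to set the formula's result against Δ. Two analysts, one following the hypotheses and one the formula, could reach opposite verdicts on the same data. Nor can this be left to a later analysis plan as a missing detail, because the article states the rule and contradicts itself.

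Three limits are fair:
- Being called inferior needs a large observed advantage, above about 0.41 to 0.43 SD. At a true advantage of 0.30 SD the probability is 12.9% (Δ = 0.22) or 9.0% (Δ = 0.24); most such trials merely fail to show non-inferiority.
- The printed interval and rule do suit the PHQ-9, where lower is better.
- The figures assume a standardised scale, whereas the printed formula is in raw score units.

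**Conclusion.** The concern holds. For the primary outcome, the interval and decision rules as printed contradict the article's own hypotheses and test the opposite claim. An app worse by exactly the margin would be declared non-inferior 99.5% (Δ = 0.22) to 99.9% (Δ = 0.24) of the time instead of 2.5%. One better by 0.30 SD would pass only 0.3% of the time at Δ = 0.22, against 99.97% under the correct rule. One better by 0.5 SD would be called inferior 77% to 83% of the time.

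These figures rest on 215 analysed per arm, SD 1, a normal approximation and literal use of the printed formula. The reversal itself depends on none of the numerical assumptions, nor on which margin is used. It should be corrected before any outcome data are analysed.

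**What to change.** Use one direction throughout and state it for each outcome. For CSE and the RS-14, choose one of:

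- **(a)** Print the interval as (μ_TAU − μ_SAENA) ± 1.96·SE and conclude non-inferiority if its upper limit is below Δ. This matches the stated alternative hypothesis. Reword the phrase that describes the difference as intervention relative to TAU. Inferiority is then an interval wholly above Δ, and an interval containing Δ is inconclusive.
- **(b)** Keep μ_SAENA − μ_TAU and conclude non-inferiority if the lower limit is above −Δ. Inferiority is then an interval wholly below −Δ, and an interval containing −Δ is inconclusive.

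For the PHQ-9, state separately that lower is better. The form SAENA minus TAU with upper limit below Δ is right only for a scale of that kind.

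The cost is a corrected formula and one sentence under (a), or two corrected sentences under (b), plus an entry in the trial registry. No extra data or participants are needed.
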